### Procedure for unblinding if needed

Not applicable.

## Data collection and management

### Plans for assessment and collection of outcomes 

Data will be collected using forms containing 20 questions each. These forms (self-administered) will be given to all participants who agree to participate in this study. The first fifteen (15) multiple-choice questions will assess theoretical knowledge and the last five (5) questions will assess practical skills based on the listening of cardiac sound recordings. Completing this questionnaire will enable to obtain for each participant, a total score, a knowledge score and a skills score during the pre-test and the post-test.

## Plans to promote participant retention and complete follow-up 

Enrolled participants of each center will be followed during the entire study period. The interest for the study will be maintained through phone calls, messages and visits during their clinical internship.

### Data management 

The data will be entered electronically using Epi Data v3.1 software. Data integrity will be enforced through a double data entry. All forms and materials related to the study will be stored in a computer with restricted access. A complete backup will be performed every month.

### Confidentiality

No personal information about enrolled participants will be shared before, during, and after the trial.

### Plans for collection, laboratory evaluation and storage of biological specimens for genetic or molecular analysis in this trial/future use

Not applicable.

### Statistical methods

#### Statistical methods for primary and secondary outcomes

The use of statistical methods will be based essentially on the comparison of participants from the two groups according to defined outcomes. The average knowledge progression of participants in the intervention group will be compared against those in the control group using Student’s t-test if the variables follow the normal distribution or by a non-parametric test if not. The average skill progression and the average total progression in knowledge and skills (based on the total progression score) of the intervention group will be compared against those of the control group using a Student’s t-test if the variables follow the normal distribution or by a non-parametric test if not. The other continuous variables (the pre-test knowledge score, the pre-test skills score, the pre-test total score, the post-test knowledge score, the post-test skills score and the post-test total score.) will also be compared using parametric or non-parametric tests. The satisfaction of all participants (ordinal variable) will be analysed using a non-parametric test.

### Interim analyses

Analyses will only be done at the end of the study.

### Methods for additional analyses (e.g. subgroup analyses)

No further analysis will be done.

### Methods in analysis to handle protocol non-adherence and any statistical methods to handle missing data

Since the primary outcome measures the total progression of participants, it is necessary for each participant to go through the entire process. Participants with missing data will be excluded from the study.

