**Methods:**

This will be a controlled study with two parallel arms (1:1). Participants (fourth-year medical students) will be divided into two groups: an intervention group (receiving additional lectures, clinical internship and audio listening sessions) and a control group (receiving additional lectures and clinical internship). At the beginning of the study, all participants will undergo a pre-test that consist of two parts: a knowledge assessment based on multiple-choice questions and a skills assessment based on recognition of cardiac sounds from audio files. Thereafter, three specific additional lectures on cardiac auscultation will be delivered and all participants will take part in their official clinical internship. During these clinical internships (eight weeks), participants of the intervention group will be invited to two listening sessions based on five digital recordings of heart sounds. At the end of the clinical internship, all participants will be invited to a post-test to evaluate their knowledge, skills and satisfaction according to their learning method. The main outcome will be the participants’ knowledge progression. The other outcomes will be the participants’ skills progression, participants’ total progression and satisfaction. Data will be collected and analyzed in per protocol.

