### Eligibility criteria 

Eligible participants must be medical students newly admitted in to the fourth year of studies and willing to participate in this study. At this stage, they will have completed only nursing training courses.

Participants who did not participate to: (i) additional lectures, (ii) clinical internship, (iii) both listening sessions (based on digital recordings of heart sounds) for intervention group only, (iv) knowledge and skills assessments and (v) those who have withdrawn their consents will be excluded.

Repeaters students will not be included.

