### Evaluation of knowledge and skills

Two evaluations (pre-test and post-test) will be organized during this study in the two groups. Each assessment will consist of two parts: a knowledge (theoretical) assessment based on multiple-choice questions and a skills (practical) assessment based on a test to recognize cardiac sounds from the audio files.

The first evaluation (pre-test, see additional file 1) will take place at the beginning of the study, directly after the recruitment of participants. The knowledge (theoretical) assessment will aim to evaluate participants’ basic knowledge and will be made on the basis of a form consisting of 15 multiple-choice questions (1 point per correct answer) validated by a scientific committee. These questions will focus on the basic anatomy and physiology of the heart, as well as the technique and semiological aspects of cardiac auscultation. The skills (practical) assessment will aim to assess the participants’ ability to recognize characteristics of cardiac sounds from audio recordings. Information on the locations of cardiac sound recording sites will be provided to participants. Participants will be invited to listen to these cardiac sound recordings using a computer connected to a loudspeaker. The five digital audio recordings selected (one normal and four pathological) will be numbered from 1 to 5. The reading sequence will be random (using a randomization tool). Each recording will be played and listened for one minute and two additional minutes will be allowed for reflection on each recording and for writing the response. Dimensions assessed will be the normal or pathological nature of a cardiac sound, timing and description of the abnormality if it is present. Each correct answer will give one point, for a total of five points.

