### Outcomes

Baseline data will consist of presenting the socio-demographic data of the learners, the pre-test knowledge score, the pre-test skills score, the pre-test total score, the post-test knowledge score, the post-test skills score and the post-test total score.

The primary outcome will be the progression of participants’ knowledge in cardiac auscultation. It will be evaluated on the basis of the difference between the participants’ knowledge score in the post-test and the participants’ knowledge score in the pre-test.

The secondary outcome will be: (i) the progression of participants’ skills in cardiac auscultation (based on the difference between the participants’ skill score in the post-test and the participants’ skill score in the pre-test), (ii) the total progression of participants’ knowledge and skills in cardiac auscultation (based on the difference between the total score obtained by the participants in the post-test and the total score obtained in the pre-test) and (iii) the participants’ satisfaction (Table 1).

**Table 1 Tab1:** Outcomes

Outcomes	Measurement	Type	Statistical analysis

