**Primary outcome**			
Progression of participants’ knowledge in cardiac auscultation.	Difference between knowledge post and pre-test score	Continue	t-test or non-parametric equivalent

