### Sample size

The minimum sample size will be calculated on the basis of a comparison of the average knowledge progression between the two groups. The hypothesis is that participants in the intervention and control groups will have an average of 30 % correct answers in the pre-tests and a 50 % increase in the intervention group compared to 10 % in the control group in the post-tests, i.e., an expected difference of 40 % between the two groups. For a power of 80 %, a ratio of 1:1 per group and an alpha error of 5 %, the minimum sample size will be 46 participants (23 per arm) [16]. Given the high risk of a refusal to participate, absenteeism and loss of sight, the minimum sample size will be increased by 20 %, for a total of 56 participants.

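### The rule excluding anyone with missing data rests on total progression, but the primary outcome is knowledge progression, so students with both knowledge scores can be lost from the primary analysis

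*Protocol article*

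**What the plan says.** The section on non-adherence and missing data has two sentences. The first gives a reason: "Since the primary outcome measures the total progression of participants, it is necessary for each participant to go through the entire process". The second gives the rule: "Participants with missing data will be excluded from the study". The rule is not limited to the outcome for which data are missing, and missing data is not defined.

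The Outcomes section reads: "The primary outcome will be the progression of participants’ knowledge in cardiac auscultation". Table 1 gives its measurement as "Difference between knowledge post and pre-test score". Total progression of knowledge and skills is listed among the secondary outcomes, with skills progression and satisfaction.

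Two other places bear on this. The Eligibility criteria list reasons for exclusion after entry, including non-participation in: "iv) knowledge and skills assessments and (v) those who have withdrawn their consents will be excluded". The satisfaction form is not in that list. The Abstract adds: "Data will be collected and analyzed in per protocol".

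**The concern.** Each student is asked for five things: a knowledge part and a skills part at the pre-test, the same two at the post-test, and a satisfaction form. The primary outcome uses two of the five. A rule that removes a student from the whole study when any of the others is missing discards usable primary data because of gaps in secondary data.

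The reason offered for the rule would make sense only if total progression were primary, because that score needs the skills parts. Under the protocol's own definition the reason falls away. Even total progression would not need the satisfaction form.

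What is at stake is precision in a small study, and possibly bias. Each arm is a different school, and the arms receive different satisfaction forms (additional files 3 and 4). If non-return differs between the schools and is related to how much a student progressed, dropping those students distorts the comparison of knowledge progression.

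**Working it through.** **1. What the primary outcome is.**

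| Place | Primary outcome |
|---|---|
| Abstract, Methods | knowledge progression |
| Outcomes section | knowledge progression |
| Table 1 | knowledge score, post-test minus pre-test |
| Sample size | sized on average knowledge progression |
| Missing-data section | total progression |

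The missing-data section stands alone against the other four.

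**2. Who is lost although both knowledge scores exist.**
- No satisfaction form: excluded by the missing-data rule alone.
- No skills part at either test: excluded by the missing-data rule and by item (iv) of the Eligibility criteria.

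**3. The plan's own sample size.** Inputs from the Sample size section: 30% correct at pre-test, rises of 50 and 10 points (so 80% against 40% at post-test), power 80%, alpha 5%, ratio 1:1. Sidedness is not stated; two-sided reproduces the figure. Two-proportion formula with pooled variance:

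n = [1.96·√(2·0.6·0.4) + 0.842·√(0.8·0.2 + 0.4·0.6)]² / 0.4² = (1.358 + 0.532)² / 0.16 ≈ 22.3, so 23 per arm and 46 in all. Power at 23 per arm is 0.81.

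Inflation: 46 × 1.2 = 55.2, so 56 in equal arms ("the minimum sample size will be increased by 20 %, for a total of 56 participants"). Power at 28 per arm is 0.885. Room for loss: (56 − 46)/56 = 10/56 = 17.9%.

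**4. Added loss under the rule.** The documents give no missing rates, so a range is assumed. Let each of the three non-knowledge parts (pre-test skills, post-test skills, satisfaction) be missing independently with probability s. The share of students with complete knowledge scores who are lost is 1 − (1 − s)³.

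| s | Lost | Left of 56 | Power | Left of 46 | Power |
|---|---|---|---|---|---|
| 2% | 1 − 0.98³ = 5.9% | 52.7 | 0.86 | 43.3 | 0.79 |
| 5% | 1 − 0.95³ = 14.3% | 48.0 | 0.83 | 39.4 | 0.75 |
| 10% | 1 − 0.90³ = 27.1% | 40.8 | 0.76 | 33.5 | 0.67 |

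Power is on the two-proportion basis that reproduces the plan's 46. The last two columns apply if the 20% allowance has already gone on refusal, absenteeism and loss to follow-up, the only losses it is said to cover.

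**5. The other end of the range.** Knowledge and skills are two parts of one 20-question form, and satisfaction is described with the post-test. If whole sittings are missed, say 5% at each, both the plan's rule and an outcome-by-outcome rule leave 56 × 0.95² = 50.5. The added loss is then near zero.

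**The case against.** The strongest reply is that the loss is probably small. A student absent from the post-test lacks the knowledge score too and is lost under either rule. A student who sits the test will normally have a skills score. What remains is chiefly an unreturned satisfaction form. This stands, and it is why the figures in the table are an upper range.

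A second reply is that the analysis is declared per protocol and that missing a skills assessment already leads to exclusion under the Eligibility criteria. This also stands in part: changing the missing-data sentence alone would leave a contradiction. It does not cover the satisfaction form, which that list omits.

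A third is that analysis sets per outcome are usually left to an analysis plan. That would answer silence. Here the article fixes a rule and supports it with a wrong description of the primary outcome.

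A reader might go further and infer that a single unanswered question removes a student, so that the weakest students are dropped selectively and many are lost over the 40 test questions. The documents do not support this. Each correct answer earns one point, so a blank simply earns none, and the section on plans for collecting outcomes treats the score as what is obtained for each participant. Moreover, 30 of the 40 questions are knowledge questions; if blanks there counted as missing, the knowledge scores would not be complete in the first place.

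**Conclusion.** The point holds. The missing-data section misstates the primary outcome and uses that misstatement to justify a study-wide exclusion that the real primary outcome does not need. Followed as written, it drops students whose two knowledge scores are complete.

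The added loss runs from near zero, if parts are missing by whole sitting, to 5.9%, 14.3% or 27.1% of those students under independent missingness of 2%, 5% or 10% per part. Both the rates and the independence are assumptions. Only towards the top of this range does the rule by itself take 56 students below 46. Bias is possible but cannot be sized from the documents; it needs non-return that differs between the schools and is related to progression. The correction is worth making because the contradiction is plain and removing it is cheap, and the case does not depend on a large expected loss.

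**What to change.** 1. In the missing-data section, change the stated reason so that it names knowledge progression as the primary outcome.
2. Replace the exclusion sentence with: *Each outcome is analysed in all participants who have the scores that outcome needs. A missing skills part or satisfaction form does not remove a participant from the knowledge analysis. An unanswered question in a completed test part scores 0.* The last sentence only clarifies what the scoring already implies.
3. Align item (iv) of the Eligibility criteria, so that missing the skills assessment does not exclude a student from the knowledge analysis.
4. Report the number missing by outcome and arm.

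The cost is a wording change before recruitment, with no extra students or data. The small downside is that the number analysed may differ between outcomes.

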### Plans to give access to the full protocol, participant level-data and statistical code

The access to the full protocol will be granted through a publication in a scientific journal.

### Oversight and monitoring

#### Composition of the coordinating center and trial steering committee

This study will be coordinated by the research team. This team is composed of 5 people and will be responsible for the main activities of the project: writing the protocol, planning and monitoring of the study, allocation and recruitment of participants, implementation of interventions, data collection, analysis of results, writing article and monitoring of publication in a scientific journal.

#### Composition of the data monitoring committee, its role and reporting structure

Two members of the research team will be permanently responsible for data collection. However, monthly meetings are planned to review the data collected.

### Adverse event reporting and harms

Not applicable.

### Frequency and plans for auditing trial conduct

All processes related to the conduct of the study will be audited by the research team on a daily basis. Monthly meetings are planned to review the progress of the study. In any case, in accordance with ethical clarity, one or two audits are planned by the regional ethics and research committee.

### Plans for communicating important protocol amendments to relevant parties (e.g. trial participants, ethical committees) 

In case of changes in the protocol, the research team is committed to submit a revised version of the ethics committee and to the Pan-African Trial Registry.

### Dissemination plans 

Four methods of dissemination will be used: (i) feedback sessions to participants, (ii) reports being submitted to faculties/universities and to Ministry of Higher Education, (iii) presentations at national and international scientific congresses and (iv) the publication in an international journal.

## Discussion

The performance of health professionals and medical students in clinical auscultation has declined over the years [7–10, 12, 13]. This decline is due to several factors, including the emergence of new diagnostic tools such as cardiac ultrasound and the ineffective teaching of clinical auscultation [7–10, 12, 13, 17].

Several learning methods have been developed to improve clinical auscultation skills of medical students and health professionals. The most common are: (i) the use of the patient simulator, (ii) the use of specialized software, (iii) the use of mobile applications and (iv) the use of devices such as the electronic stethoscope or ultrasound stethoscopes [18–29].

Patient simulators aims to facilitate learning of auscultation while overcoming some of the limitations of bedside teaching (variability of symptoms, high student-patient ratios, etc.) [18, 30]. This learning method is based on the use of a life-size manikin capable of generating synthetic cardiac sounds [12, 18, 20]. Patient simulators can improve the knowledge and skills of the learners (up to 30 %) by allowing them to listen repeatedly to cardiac sounds in conditions similar to those of the clinical environment [12, 18, 20, 31]. However, it does not allow an autonomous learning of auscultation (the manikin is often kept in the faculty). Specialized software aims to improve auscultation skills by reflecting the examination process of patients and developing learners’ integration of eyes and ears findings [19, 24, 25, 32]. This method consists of real patient’s examination filmed at the bedside, coupled with recorded cardiopulmonary sound [12, 32, 33]. Depending on the software used, a progression up to 70 % of the learners’ knowledge and skills can be observed [24, 25]. Mobile application and computer-based independent learning methods aim to facilitate the acquisition of auscultation knowledge and skills, while preserving the learner’s autonomy [14, 28, 34, 35]. It is based on the use of mobile applications or multimedia supports (CDs) which allow access to cardiopulmonary sounds and lectures [36]. The effects of this method on the knowledge of the learners are similar to those of lectures [8, 12]. However, the use of this method can reduce the teaching burden in medical schools when compared with conventional lectures [12, 29, 35]. The electronic stethoscope is often associated with software to visualize the phonograph [37]. It offers the possibility to record cardiopulmonary sounds of real patients that can be shared with one or more students or used as a teaching tool for other learning methods based on listening to audio files [37]. Moreover, the use of an electronic stethoscope instead of a traditional stethoscope during clinical internships can improve learners’ skills (up to 51.2 %) [38–40].

Digitally enhanced cardiac auscultation is designed to reinforce the classical learning method (theoretical course plus clinical internship) by adding specific lectures and supervised listening sessions based on digital recordings of heart sounds. Specific lectures will provide the background needed by learners to integrate the skills that will be acquired during clinical internships. The supervised listening sessions will provide a better understanding of the specific characteristics of cardiac sounds on the one hand and will guarantee a minimum number of repetitive listening sessions to improve the recognition of cardiac sounds on the other hand. Additional unsupervised listening sessions are recommended to complement the supervised sessions. In our approach, the absence of video content as available in some specialized software is balanced by clinical internships during which the learner will perform the cardiac examination in a practical way.

This study could contribute to the development of a learning method that takes into account the advantages of the conventional method and the contribution of digital technology. Its first added value could be learning flexibility. The learner could conduct listening sessions independently and improve his skills without depending on a patient or a teacher. The second added value could be the reinforcement of knowledge, through all the lectures and an improved integration between knowledge and skills in auscultation. Finally, the acquisition of skills related to the use of digital (electronic stethoscope or associated software) in the context of recording and sharing of cardiac sounds.

## Data Availability

All data generated and analyzed during this study will be available from the corresponding author upon reasonable request.

## Abbreviations

FMBS: Faculty of Medicine and Biomedical Sciences
HIMT: Higher Institute of Medical Technologies
